**Discussion:**

This pilot study will be the first to evaluate the role of metformin on liver fibrosis in HCV-HIV co-infected and HCV mono-infected patients with IR receiving DAA HCV treatment. If metformin is effective in reducing liver fibrosis in this patient population, this will represent a well-tolerated, easy-to-administer, inexpensive therapy that will protect against negative HCV outcomes. This study will also be an opportunity to evaluate the impact of insulin resistance and hyperglycemia on viral clearance in HCV-infected patients treated with interferon-free regimens.

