### Metformin dosing

Arm 1 participants will be provided with the following recommended dose adjustments and advised to increase the dose accordingly: week 1: 500 mg once daily (QD); week 2: 500 mg BID; week 3: 500 mg three times daily (TID); week 4: 1 g BID or 500 mg QD. Participants will also be encouraged to administer their study treatment with food whenever possible to minimize the gastric intolerances. If participants are unable to tolerate an increase in dose, they will continue on the last dose tolerated.

Metformin dosing will additionally be based on renal function and dosed as follows:if creatinine clearance (CrCl) 30–60 mL/min, metformin will be reduced to 50 % of the dose or 500 mg BIDif CrCl < 30 mL/min, metformin will be stopped.

The potential side effects associated with metformin will be reviewed with each participant.

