### Secondary outcomes

The following will be evaluated as secondary outcomes: (i) virological response rates (SVR 12 weeks post HCV antiviral therapy) will be compared between treatment groups; (ii) the change in APRI measurements from baseline to start of HCV treatment, to the end of HCV treatment (week 24) and 24 weeks post HCV treatment (week 48) will be compared between treatment groups; (iii) changes in glucose metabolism (HOMA-IR, fasting insulin, glucose levels) from baseline to 4, 8, 12, 24, 36 and 48 weeks; (iv) changes in lipid levels [total cholesterol, low-density lipoprotein cholesterol (LDL-c), high-density lipoprotein cholesterol (HDL-c), triglycerides] from baseline to 0, 12, and 36 and 48 weeks; (v) changes in anthropometric measures (waist circumference, body weight and BMI) from baseline to 0, 4, 8, 12, 24, 36 and 48 weeks; (vi) changes in liver-related inflammatory markers by (IL-6, IL-8, TNF-α, TGF-β, C-reactive protein (CRP)) from baseline to 0, 4, 8, 12, 24 and 36 weeks; (vii) changes in AFP levels from baseline to 0, 12, 24, 36 and 48 weeks; (viii) participant acceptability to study medication dosing will be assessed (in arm 1 only) at weeks 8, 24, and 48 weeks by questionnaire. Changes in scores from week 8 to end of study will be evaluated; (ix) changes in diet and physical exercise parameters from baseline to 24 and 48 weeks using dietary and physical activity questionnaires (Table 1).

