### Statistical analysis

As the primary outcome of this study, the influence of metformin on preventing and promoting regression of liver fibrosis in HCV antiviral treatment recipients will be assessed by transient elastography. The change in transient elastography scores (kPa) at week 48 (24 weeks post HCV therapy) between groups will be assessed using linear regression adjusted for baseline score. We will also compare the trend on fibrosis progression over the course of the study (12, 24, 36 and 48 weeks) between groups using mixed-effects regression analysis. All analyses will be based on intention-to-treat basis. A sensitivity analysis of the change at 48 weeks will be conducted using multiple imputations to include those participants who do not have 48-week follow-up scores.

The same set of analyses based on a per protocol basis will also be performed. For the analysis, which examines the outcome longitudinally, participants who terminated the assigned treatment prematurely will be censored at the time that they went off treatment.

Secondary outcome measures include: virological response rates, changes from baseline to week 48 in indirect measures of liver fibrosis (APRI), inflammatory markers, metabolic measures, anthropometric measurements, HCV and HIV viral loads, AFP levels and liver function. Linear regression adjusted for baseline score will be used to compare the outcome at week 48 between groups. Mixed-effects regression analysis will also be used to compare the trend over time between groups.

To account for potential confounding factors (i.e., HCV/HIV viral status, alcohol consumption, IR, BMI) associated with changes in liver fibrosis, a sensitivity analysis based on multivariate regression analysis will be performed.

Patient acceptability of daily long-term study treatment use will be evaluated (in arm 1 only) using the Treatment Satisfaction Questionnaire for Medication. Patient acceptability will be assessed based on change in median score from week 8 (first administration of questionnaire) to week 24 and week 48. Descriptive statistics will be used to summarize the data.

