### Early termination

The criteria for premature discontinuation of further study medication for an individual participant in arm 1 are as follows: treatment-related toxicity, requirement for prohibited concomitant medications, clinical reasons believed to be life-threatening by the physician, even if not addressed in the toxicity section of the protocol.

The participant will continue to be followed with the participant’s permission if the study medication is prematurely discontinued. If the participant discontinues study medication between scheduled visits, the investigator may request that the participant visit the clinic as soon as possible for lab and safety assessments and to return the study medication for accountability purposes. There will be no changes to the follow-up visit schedule, except no study medication will be administered. If the participant chooses not to remain in the study, then the participant will be withdrawn from the study and participant will be asked to come in for an early termination visit.

The criteria for permanent withdrawal from the study for an individual participant are as follows:

loss to follow-up, pregnancy or suspected pregnancy, HCV treatment required for >12 weeks, request of the participant to withdraw from the trial, any clinical AE, laboratory abnormality, intercurrent illness, other medical condition or situation occurs such that continued participation in the study would not be in the best interest of the participant, the participant is judged by the investigator to be at significant risk of failing to comply with the provisions of the protocol as to cause harm to self or seriously interfere with the validity of the trial results, progression of diabetes requiring additional diabetes medication (i.e. oral diabetes medications or insulin therapy).

In the event that the participant is withdrawn from the study due to an AE, this must be recorded on the case report form (CRF). The subject should be followed and treated by the investigator until the abnormal parameter or symptom has resolved or stabilized.

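### The change in median TSQM score from week 8 cannot show whether metformin was acceptable, and it gives no place to participants who stop it

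*Protocol article*

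**What the plan says.** Under Secondary outcomes, item (viii), the protocol article states that "participant acceptability to study medication dosing will be assessed (in arm 1 only) at weeks 8, 24, and 48 weeks by questionnaire", and then that "Changes in scores from week 8 to end of study will be evaluated". Table 1 agrees: the TSQM is scheduled for arm 1 at weeks 8, 24 and 48 and at no other visit. The Statistical analysis section sets the criterion: "Patient acceptability will be assessed based on change in median score from week 8 (first administration of questionnaire) to week 24 and week 48". It adds "Descriptive statistics will be used to summarize the data". No test and no threshold for acceptable is given.

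Three other sections bear on the point.
- Metformin dosing describes a dose increase over weeks 1 to 4, keeps a participant who cannot tolerate a step on the last tolerated dose, and expects some intolerance: "Participants will also be encouraged to administer their study treatment with food whenever possible to minimize the gastric intolerances".
- Early termination lists treatment-related toxicity as a reason to stop study medication. Participants who stop are followed if they agree: "There will be no changes to the follow-up visit schedule, except no study medication will be administered". Those who choose to leave the study are asked to attend an early termination visit.
- Multiple imputation is named in the Statistical analysis section for the primary outcome at week 48 only.

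**The concern.** Acceptability is a question of level: how satisfied are participants with the drug, and how many are still willing to take it? The stated criterion answers a different question, namely whether the group median moved after week 8. There is no score before treatment and no control arm, so nothing anchors that movement. Stopping the drug, the plainest sign that it was not acceptable, does not enter the measure.

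A difference between two group medians also depends on who contributes to each. If the people behind the week 48 median are a more satisfied subset of those behind the week 8 median, the difference is partly or wholly selection. A flat or rising median could then be read as good acceptability when it shows neither a high level nor an improvement in anyone.

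**Working it through.** **Inputs from the protocol article.** TSQM at weeks 8, 24 and 48, arm 1 only. Arm size from Sample size calculation: 24 per group with 20 % loss, 24 / (1 − 0.20) = 30, which reproduces the planned 24 + 6. No figure is stated for the TSQM itself.

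**Assumptions, not in the article.** Scores roughly normal with mean 65 and SD 20, within-person correlation 0.7, and no true change in anyone.

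**Step 1: what a change of 0 means.** If all participants score low at every visit, the change is low − low = 0. If all score high, it is high − high = 0. The criterion gives the same result in both cases. This step needs no assumption about drop-out.

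**Step 2: largest shift from selective loss after week 8.** If the lowest fraction f leaves, the median of the rest is the (1 + f)/2 quantile of the original distribution. The shift is z × SD.
- f = 0.10: quantile 0.55, z = 0.126, shift 0.126 × 20 = 2.5 points.
- f = 0.20: quantile 0.60, z = 0.253, shift 0.253 × 20 = 5.1 points.

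**Step 3: simulation of a 30-person arm, no true change.** In the selective scenarios, the participants with the lowest stable satisfaction leave.

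| Loss before week 8 | Loss after week 8 | Median week 8 | Median week 48 | Change, those available | Change, same completers |
|---|---|---|---|---|---|
| 0 | 10 % | 65.0 | 67.5 | +2.5 | about 0 |
| 0 | 20 % | 65.0 | 69.9 | +4.9 | about 0 |
| 10 % | 0 | 67.5 | 67.5 | about 0 | about 0 |
| 20 % | 0 | 69.8 | 69.9 | about 0 | about 0 |
| 10 % | 10 % | 67.5 | 69.8 | +2.3 | about 0 |
| 20 % | 20 % | 69.8 | 74.6 | +4.8 | about 0 |

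With random loss the change is about 0 in every row.

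**Reading.** Only selective loss after week 8 moves the stated criterion. Selective loss before week 8 raises the week 8 reference by about 2.5 to 5 points and leaves the change at about 0. Comparing the same people at both visits removes the spurious change, but not the inflated level (74.6 against a true 65 in the last row). The level therefore has to be read beside the number who stopped. The completer result holds for leaving that depends on stable satisfaction. If leaving followed a passing low score at week 8, completers would show a small fall through regression to the mean.

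**The case against.** The strongest case against the point has four parts.

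*The level is not hidden.* A change in medians cannot be computed without the medians, and descriptive summaries are promised. That is so, but the article still names the change as the basis for judging acceptability, and an analysis plan that follows it would carry that forward.

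*The choice of people may be settled elsewhere.* The wording under Secondary outcomes is compatible with within-person change, and an article may leave the analysis set to the full protocol or the analysis plan. This stands, and it is why the selection effect is stated conditionally. The failure to measure level does not depend on it.

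*Starting at week 8 is defensible.* The stated interest is long-term daily use. Early intolerance is recorded elsewhere: adverse events from randomization, drug accountability at weeks 4 and 8, an 80 % adherence rule, and a subgroup analysis by full dose or not. This also stands, so a week 4 questionnaire is a preference and not a correction. None of these records is linked to acceptability, however.

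*The size is an extreme case.* SD 20 and loss of only the lowest scorers are assumptions. The 20 % in Sample size calculation is an allowance for loss to follow-up in both arms over the whole study; it is not a forecast of dissatisfied metformin users leaving after week 8. The figures are therefore upper bounds under the assumed SD.

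A reader might go further and infer that those who stop during dose escalation never count, and that the measure makes metformin look acceptable by design. The article does not support this. Not tolerating a step leads to staying on the last tolerated dose, those who stop remain on the visit schedule if they agree, and nothing says they skip the TSQM. Early loss leaves the change at about 0, so the two mechanisms do not add up on the stated criterion. A reader might also tie the TSQM to the Abstract's statement that "this will represent a well-tolerated, easy-to-administer, inexpensive therapy that will protect against negative HCV outcomes". That sentence is conditional on metformin reducing fibrosis and does not refer to the questionnaire.

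**Conclusion.** The point holds in a limited form. As a criterion for acceptability, the change in median TSQM from week 8 is uninformative about level and silent on stopping; both follow directly from the stated definition. The possible spurious rise of up to about 2.5 points (10 % loss) or 5 points (20 % loss) depends on medians taken over available participants, fully selective loss after week 8 and an assumed SD of 20. It is about 0 if loss is random or if the same people are compared under the simulated conditions. The article does not show that a bias will occur, or in which direction early stopping would act on the change. The matter is minor: one single-arm, descriptive secondary outcome without a test or threshold, with no bearing on the primary analysis.

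**What to change.** In the Statistical analysis section, and to match under Secondary outcomes item (viii), replace the change in median as the criterion with the following.

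1. The TSQM level (median and spread) at weeks 8, 24 and 48, with the number scored at each visit.
2. Beside it, with all participants randomized to arm 1 as denominator, the number and proportion still taking metformin at each of those visits, and the number who stopped or reduced it, by week and reason, including weeks 0 to 8.
3. Change from week 8 only as within-person change in participants scored at both visits, labelled as such.

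The cost is a change of wording and one small table. The TSQM, drug accountability and adverse event data are already on the schedule. A TSQM at the existing week 4 visit or at discontinuation would add information on early experience for about 30 participants, at the price of one further short questionnaire each time; it is optional.

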The effect of DAA HCV treatments on insulin resistance and long-term risk of type 2 diabetes has yet to be clearly established. A randomized controlled trial of HCV mono-infected study participants receiving 14 days of monotherapy with the protease inhibitor danoprevir, found that serum HCV RNA and homeostatic model assessment of insulin resistance (HOMA-IR) correlated significantly (Spearman rho = 0.379, *p* < 0.0001) [16]. At the end of 14 days of danoprevir monotherapy the mean decrease in HCV RNA was 2.2 ± 1.3 log10 IU/ml (*p* < 0.0001) in patients who received the active drug (*n* = 40), which correlated with a decrease in mean HOMA-IR score by 1.6 ± 1.1 (*p* < 0.0001). In contrast, HCV-RNA and HOMA-IR remained unchanged in placebo recipients. The role of insulin resistance and hyperglycemia as predictors of SVR with DAA HCV treatment has not been clearly established. There are also no studies to date that have examined the role insulin resistance or hyperglycemia play in promoting progression or preventing regression of liver fibrosis in patients that have achieved SVR with HCV antiviral therapy.

In high-risk populations, metformin, an insulin sensitizer, has been shown to delay or prevent the onset of T2DM [17]. While it is unknown whether this specific benefit extends to those infected with HCV, metformin does improve HCV treatment and liver-related outcomes. At least one study showed treatment with metformin resulted in higher SVR rates when compared with the control group (59.2 % vs. 38.8 %, chi-square 4.083, *p* = 0.043) [18]. HCV-infected patients with cirrhosis and T2DM who were taking metformin had a decreased risk of developing HCC [19, 20].

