Baseline characteristics will be expressed as mean and standard deviation (SD) for continuous variables and percentages for categorical variables. Baseline variables to be considered include: age, gender, ethnicity, HCV genotype and viral load, HIV viral load and CD4 count (as per SOC), HbA1c, HOMA-IR, FibroScan® scores, smoking history, alcohol consumption, and illicit drug use.

Lifestyle modification will be evaluated through changes in physical activity (changes in median MET/week, percentage change in participants classified as low, medium and high level of activity) and dietary changes (change in median daily caloric intake, daily consumption of fat, protein, carbohydrates and micro/macro nutrients). Linear regression adjusted for baseline score will be used to compare the outcome at week 48 between groups. Mixed-effects regression analysis will also be used to compare the trend over time between groups.

Data will be collected on liver-related complications (progression of liver fibrosis stage, HCC, transplantation) and mortality. We anticipate that the event rate will be low given the small sample size and short duration of follow-up.

Subgroup analyses will be conducted based on SVR to compare the effect virological response influences liver fibrosis and the benefit of metformin in reducing progression of fibrosis. Subgroup analyses will also be conducted based on HIV status to compare the influence of HIV infection on progression of liver fibrosis and benefit of metformin in reducing the progression of fibrosis.

Subgroup analyses based on metformin doses (full dose versus not) in the metformin group and weight loss in patients in both treatment arms will also be conducted. These additional analyses will be useful in determining if lower doses can achieve the same benefit and the impact that potential weight loss associated with this medication may have on steatosis and improving liver outcomes respectively.

Subgroup analyses will also be conducted based on end of study HOMA-IR score (<2 vs. > 2) to evaluate if the benefits of metformin are dependent or independent of the insulin-sensitizing effects of this treatment.

As a sensitivity analysis, we will also consider using multiple imputation techniques to impute missing data for the primary outcome at 48 weeks. Linear regression adjusted for baseline score will then be used to compare the groups.

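### Subgroups defined after randomisation (SVR, weight loss, end-of-study HOMA-IR) and by achieved dose cannot answer the mechanism and dose questions set for them

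*Protocol article*

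**What the plan says.** Under Statistical analysis, the protocol article lists subgroup analyses on five variables. HIV status is a baseline stratification factor and is not at issue. The other four are:

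- **SVR:** "Subgroup analyses will be conducted based on SVR to compare the effect virological response influences liver fibrosis and the benefit of metformin".
- **Dose and weight loss:** "Subgroup analyses based on metformin doses (full dose versus not) in the metformin group and weight loss in patients in both treatment arms". The purpose given for dose is: "These additional analyses will be useful in determining if lower doses can achieve the same benefit".
- **End-of-study HOMA-IR, below versus above 2:** "Subgroup analyses will also be conducted based on end of study HOMA-IR score". The purpose given is to see whether the benefit of metformin depends on its insulin-sensitising action.

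Other sections show how the article regards these variables:

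- Secondary outcomes, item (i): "virological response rates (SVR 12 weeks post HCV antiviral therapy) will be compared between treatment groups". The Background cites a study in which "treatment with metformin resulted in higher SVR rates when compared with the control group" (59.2 % vs 38.8 %).
- Changes in HOMA-IR and in body weight are secondary outcomes (iii) and (v). The subgroup text itself links weight loss to metformin.
- Under Metformin dosing, the dose reached depends on what the participant tolerates and on creatinine clearance.
- Under Selection of participants, entry requires a HOMA-IR above 2.0 at screening.

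**The concern.** A subgroup comparison of randomised arms is fair when membership is fixed before treatment starts. If treatment can move patients across the boundary, the arms no longer contain like patients within a subgroup.

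End-of-study HOMA-IR shows this most clearly. Everyone starts above 2. A control participant who ends below 2 got there without metformin, whereas a metformin participant may have got there because of it. The two are different kinds of patient, and any difference in their kPa mixes drug effect with selection. The same reasoning applies to weight loss, and to metformin benefit within SVR strata.

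The dose split fails for a different reason. It lies wholly within arm 1, with no randomised comparator, and those on lower doses are there because of intolerance or renal function. This is confounding by whatever set the dose.

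At stake are the two questions these splits are meant to answer: whether benefit runs through insulin sensitisation, and whether lower doses do as well. Following the plan exactly could produce an answer to either with no true effect behind it.

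**Working it through.** **1. The plan's own figure.** Inputs from Sample size calculation: difference 4 kPa, SD 4.8, 24 per group. Two-sided alpha 0.05 is assumed. Noncentrality = 4 / (4.8 × √(2/24)) = 2.89; the two-sample t-test on 46 df gives 80.7 % power. Allowing for loss, 24 / (1 − 0.20) = 30 per group, 60 in total. The plan's figures reproduce, so 4.8 and 4 kPa serve as the scale below.

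**2. When each variable is known.**

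| Variable | Known | What sets it |
|---|---|---|
| HIV status | before randomisation | baseline, stratified |
| SVR | 12 weeks after HCV treatment | secondary outcome (i) |
| Weight loss | during follow-up | secondary outcome (v) |
| End-of-study HOMA-IR | end of study | secondary outcome (iii) |
| Achieved dose | after titration, arm 1 only | tolerance, renal function |

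**3. Size for the HOMA-IR split, no true effect on kPa.** The article gives neither the HOMA-IR/kPa correlation (ρ) nor the effect of metformin on HOMA-IR (s, in SD units), so both are assumed. Let H be the standard-normal HOMA-IR a patient would have without metformin. Metformin shifts it to H − s, and the cut is placed at the control median. The spurious difference (metformin minus control) is 4.8 × ρ × ΔH, where φ and Φ are the standard normal density and distribution functions:

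- low stratum: ΔH = φ(0)/0.5 − φ(s)/Φ(s)
- high stratum: ΔH = φ(s)/(1 − Φ(s)) − φ(0)/0.5

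For s = 0.5: low 0.798 − 0.352/0.691 = 0.289; high 0.352/0.309 − 0.798 = 0.343.
For s = 1.0: low 0.798 − 0.242/0.841 = 0.510; high 0.242/0.159 − 0.798 = 0.727.

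| s | ρ | Low stratum (kPa) | High stratum (kPa) |
|---|---|---|---|
| 0.5 | 0.3 | 0.42 | 0.49 |
| 1.0 | 0.3 | 0.73 | 1.05 |
| 0.5 | 0.5 | 0.69 | 0.82 |
| 1.0 | 0.5 | 1.22 | 1.75 |

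Metformin looks worse in both strata although it does nothing to kPa. A simulation of 2,000,000 patients per scenario agrees, with a whole-sample difference of about 0. With ρ = 0 or s = 0 the bias is 0.

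**4. With the planned baseline adjustment.** The article's week-48 method is linear regression on baseline score. A further simulation added baseline kPa, with an assumed baseline/final correlation of 0.5 to 0.8 and the same ρ with both measurements. The smallest within-stratum bias is about 0.1 kPa (ρ = 0.3, s = 0.5, baseline/final 0.8). The largest is about 1.05 kPa (ρ = 0.5, s = 1.0, baseline/final 0.5). Against 4 kPa that is 0.1/4 = 2.5 % to 1.05/4 = 26 %.

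**5. Dose split, no true dose effect.** Assume 70 % reach full dose and the factor behind tolerability correlates 0.3 to 0.5 with kPa. The normal density at the 70 % point is 0.348, so the gap is 4.8 × ρ × (0.348/0.7 + 0.348/0.3) = 4.8 × ρ × 1.656: 2.4 kPa at 0.3 and 4.0 kPa at 0.5. This is unadjusted for baseline, and is 0 if the correlation is 0.

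**6. Precision.** With 12 completers per arm per stratum, the standard error of an interaction is 4.8 × √(4/12) = 2.77. Power for a 4 kPa interaction is Φ(4/2.77 − 1.96) = Φ(−0.52) = 30 %.

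**The case against.** The strongest defence is that this is a self-described pilot. The subgroup sentences state purposes and draw no conclusions, and an exploratory label is the sort of thing a full protocol or analysis plan supplies. That is fair as far as it goes. However, the article fixes both the splits and the questions they are meant to settle, and a label elsewhere would not make these contrasts answer them.

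Several stronger readings are tempting, and the documents do not support them:

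- **That all four variables are results metformin changes relative to control.** Dose is not. It exists only in arm 1, and its problem is confounding by tolerance and renal function.
- **That the whole SVR analysis is unsound.** Its first aim, how virological response relates to fibrosis, is a legitimate prognostic question. Only metformin benefit within SVR strata is open to criticism.
- **That 0.4 to 1.7 kPa is the bias of the plan as written.** That range omits the baseline adjustment given under Statistical analysis, which is the natural reading for the subgroups too. Adjustment shrinks the bias but does not remove it.
- **That the per-protocol censoring shares the fault by acting on arm 1 alone.** The text censors those for whom "participants who terminated the assigned treatment prematurely will be censored at the time that they went off treatment" applies, without restriction to an arm. Arm 2 is assigned lifestyle treatment, and intention-to-treat already comes first. Asymmetry may be likely, but it is an inference and is not part of this point.

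**Conclusion.** The point holds, confined to the secondary subgroup analyses. Arm contrasts within strata of SVR, weight loss or end-of-study HOMA-IR, and the dose contrast within arm 1, are not randomised comparisons. They cannot show whether benefit depends on insulin sensitisation or whether lower doses do as well. That follows from the article's own text and needs no assumption.

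The size does need assumptions, since the article gives neither the correlation nor the HOMA-IR effect. For the HOMA-IR split it runs from zero up to about 1.05 kPa with baseline adjustment, or about 1.7 kPa without, over the ranges shown. A correlation of zero would sit badly with the Background, which calls insulin resistance a major determinant of liver fibrosis.

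A reader might infer that the trial's main result is compromised. It is not: the primary week-48 comparison is by randomised arm on an intention-to-treat basis.

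**What to change.** - Test effect modification only in subgroups defined at baseline, with an arm-by-factor interaction term: HIV status as planned, and baseline HOMA-IR in place of end-of-study HOMA-IR. Because everyone enters above 2, baseline HOMA-IR is better used as a continuous modifier than cut at 2.
- Report kPa by SVR, weight loss and achieved dose descriptively, labelled exploratory and non-randomised, without arm contrasts.
- Delete the aims of judging whether lower doses give the same benefit and whether benefit depends on insulin sensitisation.
- If mechanism remains of interest, specify one exploratory mediation analysis. Use the week-12 change in HOMA-IR or weight as mediator (Table 1 already schedules fasting insulin, glucose and anthropometry then), adjusted for baseline covariates. State its assumption of no unmeasured mediator-outcome confounding. In about 48 completers it would be imprecise.

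The cost is analysis wording and a little programming, with no new data. The trial gives up any formal claim on dose, on mechanism or on metformin benefit by SVR. Baseline interaction tests will also have low power (30 % for 4 kPa under an even split), so they too should be read as exploratory.

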### Sample size calculation

To date there have been no studies that have investigated the benefits of improved IR in the HIV-HCV co-infected population or in HCV mono-infected patients. Studies that have investigated the effects of HCV antiviral therapy on FibroScan® score reported a 32 % reduction in mean score (10.6 +/- 4.8 kPa) compared with baseline in patients that obtained a treatment response [37]. Based on these study results, a sample size of 24 participants in each group would provide approximately 80 % power to detect a 4 kPa difference between the two treatment arms assuming a similar standard deviation. We anticipate a 20 % loss to follow-up, so an additional six participants will be randomized per group to account for loss to follow-up and to allow secondary outcome analyses. Using regression of the final measurement on the initial measurement will likely improve the power relative to using simple difference scores.

All analyses will be based on intention-to-treat basis and per protocol analysis. Intention-to-treat population will be defined as the set of all patients randomized.

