When half (n = 30) of the participants have completed their 48-week visit, an interim analysis of efficacy will be conducted. The same technique and analytic strategy will be used to analyze the primary end point, transient elastography score (kPa) at 48 weeks. An intention-to-treat approach will be taken, linear regression adjusting for baseline score, and missing imputations to account for missing data will be used. The O’Brien-Fleming approach using the Lan-DeMets alpha spending function will be used, so that the criterion for statistical significance at the first analysis will be 0.005 and the criterion at the final analysis will be 0.048 to maintain 80 % power overall. This analysis will be supplemented by a mixed-effects regression model examining the outcome at all time points for all patients available, and adjusting for baseline values.

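### The interim and final criteria of 0.005 and 0.048 do not follow from the Lan-DeMets spending function the plan names, at either end of its own information range (50 % to 62.5 %)

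*Protocol article*

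**What the plan says.** The last paragraph of the Statistical analysis section sets the interim look: "When half (n = 30) of the participants have completed their 48-week visit, an interim analysis of efficacy will be conducted". The method is O'Brien-Fleming, and this "approach using the Lan-DeMets alpha spending function will be used". The paragraph presents the criteria as the result of that method: "the criterion for statistical significance at the first analysis will be 0.005 and the criterion at the final analysis will be 0.048". Their stated purpose is power: "the criterion at the final analysis will be 0.048 to maintain 80 % power overall". It gives neither an overall alpha nor an information fraction.

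The Sample size calculation section powers the trial on 24 participants per group. It expects a 20 % "loss to follow-up, so an additional six participants will be randomized per group", so 60 are randomised and 48 are expected to have week-48 data.

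The interim paragraph says the approach to the primary endpoint is unchanged at the interim, and then adds that "missing imputations to account for missing data will be used". Elsewhere in the same section, multiple imputation of the week-48 score is a sensitivity analysis.

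**The concern.** The paragraph fixes a method, a trigger and two numbers, and the three do not agree. A spending function produces its bounds from the information fraction at the look. Here the bounds are printed as constants and look like those of a different, fixed-schedule method. The trigger counts completers but calls 30 of them half, which divides completers by everyone randomised. The plan's own attrition assumption implies a smaller denominator.

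At stake is which bound governs an efficacy claim. At 50 % information an interim p of 0.004 meets the printed criterion but not the named function's. At 62.5 % a p of 0.008 meets the named function's criterion but not the printed one. At the final analysis, a p between 0.048 and 0.0490 (50 %) or between 0.0471 and 0.048 (62.5 %) is significant under one reading only. In an open-label trial, a choice between these readings made after the data are seen would be open to challenge.

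**Working it through.** **Inputs.** Two looks; printed criteria 0.005 and 0.048; interim at 30 week-48 completers (Statistical analysis). 24 per group evaluable, 20 % loss, difference 4 kPa, SD 4.8 kPa (Sample size calculation). Assumption: overall two-sided alpha 0.05, i.e. 0.025 per side.

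**Sample size first.** The normal approximation gives 23 per group. At the stated 24, power is 0.823 (normal) or 0.807 (t). Allowing for loss, 24/0.8 = 30 per group. The plan's sample size reproduces.

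**Information fraction at the trigger.** With no loss, t = 30/60 = 0.50. With the planned 20 % loss, t = 30/48 = 0.625. The plan's range is therefore 50 % to 62.5 %.

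**Boundaries.** The two test statistics are bivariate normal with correlation √t.

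- *Lan-DeMets, O'Brien-Fleming type, 0.025 per side.* Interim two-sided level = 2 × 2{1 − Φ(z₀.₉₈₇₅/√t)}, with z₀.₉₈₇₅ = 2.2414. At t = 0.50, 2.2414/0.7071 = 3.170, giving 0.0031. At t = 0.625, 2.2414/0.7906 = 2.835, giving 0.0092. The final critical value c₂ solves 1 − P(|Z₁| < c₁, |Z₂| < c₂) = 0.05.
- *Classical O'Brien-Fleming.* Critical values are c/√t and c. At t = 0.50, c = 1.9774, so the interim value is 1.9774/0.7071 = 2.797.
- *Same spending function applied directly to two-sided 0.05 (less usual).* Interim level = 2{1 − Φ(1.96/√t)}.

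| Method | t | Interim | Final |
|---|---|---|---|
| Printed in the plan | not stated | 0.005 | 0.048 |
| Classical O'Brien-Fleming | 0.50 | 0.0052 | 0.0480 |
| Lan-DeMets, 0.025 per side | 0.50 | 0.0031 | 0.0490 |
| Lan-DeMets, 0.025 per side | 0.55 | 0.0050 | 0.0484 |
| Lan-DeMets, 0.025 per side | 0.625 | 0.0092 | 0.0471 |
| Lan-DeMets, direct two-sided | 0.50 | 0.0056 | 0.0478 |
| Lan-DeMets, direct two-sided | 0.625 | 0.0132 | 0.0450 |

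The classical boundary at half information reproduces the printed pair. The named function does so only near t = 0.55. The direct two-sided form at t = 0.50 is close, but 0.0056 does not round to 0.005.

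**Error and power of the printed pair.** Overall two-sided type I error is 0.0499 at t = 0.50 and 0.0492 at t = 0.625. With 48 evaluable, 4 kPa and SD 4.8:

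| t | Power, printed | Power, Lan-DeMets | Early crossing, printed | Early crossing, Lan-DeMets |
|---|---|---|---|---|
| 0.50 | 0.820 | 0.822 | 22 % | 18 % |
| 0.625 | 0.820 | 0.819 | 30 % | 37 % |

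**The case against.** The best defence is that the printed pair lies inside the plausible range. The plan states no information fraction, so reading it as exactly 50 % is an inference from the word half and from the match with the classical boundary. At t = 0.55 the named function gives 0.0050/0.0484, which rounds to the printed figures. A 10 % loss would put the look close to that point: 30/54 = 0.556, giving 0.0053/0.0483. This stands as arithmetic. It does not rescue the text, because neither 55 % information nor 10 % loss appears in the plan, and the trigger is described as half.

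Four stronger readings are tempting, and the document does not support them.

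- *The bounds inflate the false-positive rate.* They do not; overall error is at or below 5 % at both ends of the range.
- *The look will occur at 62.5 % information.* That holds only if the full 20 % loss occurs. The interim criterion is about 1.6 times too liberal at 50 % (0.005/0.0031) and about 1.8 times too strict at 62.5 % (0.0092/0.005). These errors run in opposite directions and cannot both apply.
- *A given interim p would stop the trial.* The paragraph sets a criterion for significance and states no stopping rule.
- *The two looks are different tests, because imputation appears in the interim analysis.* That is one reading of a condensed sentence. It may equally compress the baseline-adjusted regression and its imputation sensitivity analysis. It is an ambiguity to clear up, not a demonstrated inconsistency.

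**Conclusion.** The point holds as a mismatch between the named method and the printed criteria. If overall two-sided alpha is 0.05, the Lan-DeMets O'Brien-Fleming-type function gives 0.0031/0.0490 at 50 % information and 0.0092/0.0471 at 62.5 %. Neither is the printed 0.005/0.048, which is the classical equally spaced pair. The phrase about power also misstates what such bounds protect: they hold type I error.

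The practical size is small. The final criterion moves by about 0.001 either way, power by no more than about 0.002, and the chance of crossing early by 4 to 7 percentage points. What remains is uncertainty over which bound decides an efficacy claim. Severity is minor to moderate. The conclusion rests on the alpha assumption and on information being proportional to the number of week-48 scores, with imputation adding little.

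**What to change.** Choose one of two wordings before any interim data are seen.

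(a) Keep Lan-DeMets O'Brien-Fleming-type spending and state a two-sided alpha of 0.05. Drop the fixed figures and compute both bounds at the observed information fraction: week-48 scans at the interim over those expected at the final analysis, planned as 48. Give 0.0031/0.0490 (50 %) and 0.0092/0.0471 (62.5 %) as examples.

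(b) Name the classical O'Brien-Fleming boundary, state a two-sided alpha of 0.05, keep 0.005/0.048, and time the look at half of the expected week-48 data, about 48/2 = 24 completers.

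In either case, replace the power phrase with a statement that the bounds hold the overall two-sided type I error at 5 %. Also state that both looks use the same primary model with the same handling of missing week-48 scores.

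The cost is protocol and analysis-plan wording only, with no added participants. Option (b) also brings the look forward by about six completers.
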